## Abstract

**Background:**

The prevalence of significant obstructive coronary artery disease with complex lesions is high in patients who have low extremity artery disease (LEAD). However, intermediate- or long-term cardiovascular prognosis of LEAD patients undergoing percutaneous transluminal angioplasty (PTA) remains poor. Accordingly, prophylactic coronary revascularization may modify short- and long-term cardiovascular outcomes of LEAD patients receiving PTA. Because myocardial ischemic symptoms are often masked in LEAD and the accuracy of non-invasive stress tests is usually limited, a high-quality randomized controlled trial aimed at the investigation of the prognostic role of coronary evaluation strategies before PTA is warranted.

**Methods/Design:**

The proposed study is designed as a prospective, multi-center, open-label, superiority, randomized controlled trial. The study is conducted in high-volume centers for PTA and coronary revascularization in Taiwan. To meet the inclusion criteria, the patients must be at least 20 years old, have known LEAD, and have been admitted for elective PTA. We plan to enroll 450 participants who are randomly allocated to a routine group (routine coronary angiography without a previous non-invasive stress test before PTA) and a selective group (selective coronary angiography based on the results of non-invasive stress tests before PTA) with 1:1 ratio. Besides, we expect to enroll about 250 additional participants, who are not willing to be randomly assigned, in the registration group. The choice of revascularization procedure depends on the operator’s or cardiovascular team’s suggestion and the patient’s decision. Clinical follow-up will be performed 30 days after PTA and every 6 months until the end of the 1-year follow-up for the last randomly assigned participant. The primary endpoint is the composite major adverse cardiac event on long-term follow-up. Pre-specified secondary and other endpoints are also evaluated. Those assessing biomarkers and clinical endpoints are all blinded after assignment to interventions.

**Discussion:**

The results of the trial will, for the first time, support better decision-making for coronary evaluation before PTA in LEAD. If favorable, routine coronary angiography followed by revascularization will improve cardiovascular outcomes in LEAD patients undergoing PTA.

**Trial registration:**

ClinicalTrials.gov identifier: NCT02169258 (registered on 21 June 2014); registry name: Routine Coronary Catheterization in Low Extremity Artery Disease Undergoing Percutaneous Transluminal Angioplasty (PIROUETTE-PTA).

**Electronic supplementary material:**

The online version of this article (doi:10.1186/s13063-016-1237-0) contains supplementary material, which is available to authorized users.

## Background

Patients with low extremity artery disease (LEAD) have a high risk of death from cardiovascular cause [1]. The existence and severity of coronary atherosclerosis are known to be correlated to those of peripheral artery disease [2–5]. The prevalence of significant obstructive coronary artery disease (CAD) is high (up to 70 %) in patients who have LEAD [2, 6]. Besides, complex coronary artery lesions are more common in patients with LEAD than in those without [5]. Furthermore, patients with concomitant LEAD are prone to have a greater chance of coronary disease progression [7]. Since myocardial infarction is a major cause of peri-operative death in vascular surgery [6], substantial efforts, such as risk stratification and routine or selective coronary angiography/revascularization before vascular surgery [8–11], have been made in order to improve cardiovascular outcome during operation. Despite inconsistent results in previous clinical studies [12–14], a recently published prospective randomized controlled trial (RCT) with 208 enrolled cases showed that a strategy of routine coronary angiography positively impacts long-term outcome of patients with peripheral artery disease at medium-high risk for vascular operation [6]. Nevertheless, coronary angiography/revascularization is recommended only in some clinical situations before vascular surgery by clinical guidelines [15–17].

Percutaneous transluminal angioplasty (PTA) is usually the first choice of revascularization for the majority of patients with LEAD in the current era. However, intermediate- or long-term prognosis of LEAD patients undergoing PTA remains poor; the average rate of total mortality is 25 % and the average rate of cardiovascular death is 12 % [18–21]. CAD is an independent predictor of total mortality after PTA [18]. Furthermore, ischemia/reperfusion injury after PTA can cause systemic inflammatory response [22, 23], probably leading to peri-procedural cardiovascular mortality in the existence of significant CAD [24]. Interestingly, silent ischemia is common in patients with LEAD because of the high prevalence of diabetes mellitus and inactivity in such patients. A commonly used stress test, the treadmill exercise test, for screening the existence of CAD is usually unsuitable in patients with LEAD because intermittent claudication with resultant limited activity or in bedridden status is frequently present due to severe peripheral artery disease. Furthermore, the accuracy of the available stress tests, including the treadmill exercise test, dobutamine stress echocardiography (DSE), or dipyridamole thallium 201 myocardial perfusion scintigraphy (dTS), is not so high (around 70–75 %), probably hampering vulnerable cases from receiving beneficial revascularization therapy, especially in asymptomatic CAD. Accordingly, prophylactic coronary revascularization may modify short- and long-term cardiovascular outcomes of LEAD patients receiving PTA. However, there is no RCT aimed at the investigation of the prognostic role of routine angiography and revascularization before PTA for LEAD. In addition, it has never been mentioned in the clinical guidelines. Therefore, there is substantial variability in practice strategies among interventionists. Taken together, further investigation of the clinical role of routine screening for the presence of CAD with subsequent revascularization has strong rationality and is deemed mandatory in LEAD patients undergoing PTA.

In this principal investigator-initiated prospective RCT, the PIROUETTE-PTA (Prognostic Impact of Routine Coronary Catheterization in Low Extremity Artery Disease Undergoing Percutaneous Transluminal Angioplasty) Study investigators will evaluate the prognostic effects of routine coronary angiography (routine strategy) versus selective coronary angiography based on the results of non-invasive stress tests (selective strategy) or conservative management (real-world strategy) before PTA for LEAD. The potential mechanisms will be elucidated. We hypothesize that a strategy of routine coronary angiography will positively impact long-term outcome as well as favorable cost-effectiveness, being superior to “selective strategy” or “real-world” strategy, in LEAD patients receiving PTA.

## Methods/Design

### Study design

The proposed study is designed as a prospective, multi-center, open-label, superiority RCT. This study protocol with amendment (version 5.0; 25 May 2014) has been approved by the institutional review board (IRB) of National Cheng Kung University Hospital (identifier: B-BR-103-023) and has been registered in ClinicalTrials.gov (identifier: NCT02169258). Provisions of all items from the World Health Organization Trial Registration Data Set can be found in this protocol and at www.clinicaltrials.gov. This study conforms to CONSORT (Consolidated Standards of Reporting Trials) 2010 guidelines for RCTs [25] and CONSORT extension for trials assessing non-pharmacologic intervention [26] (Additional file 1). The study protocol also fulfills SPIRIT (Standard Protocol Items: Recommendations for Interventional Trials) 2013 guidelines [27]; Additional file 2 shows this in more detail. All study participants give informed consent and this study follows the regulation of the ethics committee of the National Cheng Kung University Hospital. Any modifications to the protocol will require a formal amendment approved by the IRB of National Cheng Kung University Hospital and other participating sites. The investigators and study nurses will fully explain the study protocol and get the informed consent back from potential trial participants or authorized surrogates. An additional signed consent form must be obtained from all participants in sub-studies if information with respect to sample collection is not covered in the original informed consent form for the main PIROUETTE-PTA study. The study is conducted in high-volume centers (either academic medical centers or regional hospitals) for PTA and coronary revascularization in Taiwan. Reference to where list of study sites can be obtained at www.clinicaltrials.gov.

### Participants and eligibility

This prospective RCT will consecutively enroll about 700 (450 randomly assigned and estimated 250 in registration strategy) eligible patients (≥20 years old) who have known LEAD (documented by previous angiography or sonography) and were admitted for elective PTA. The flow diagram is shown in Fig. 1. The definition of LEAD will be the presence of significant stenosis (≥70 % narrowing as compared with the reference vessel size), including total occlusion, in at least one major artery in the low extremities. Subjects are excluded if they have at least one of the following situations before screening: known CAD or unstable angina within the past 3 months, acute myocardial infarction within the past 6 months, known CAD having received percutaneous coronary intervention (PCI) or bypass surgery within the past 6 months, plan to do bypass surgery for known LEAD, pregnancy, documented active malignancy, and need for emergency PTA. The inclusion and exclusion criteria are listed in Table 1.

**Fig. 1 Fig1:**
[figure not shown]
Participant flow diagram. *PTA* percutaneous transluminal angioplasy

**Table 1 Tab1:** Eligibility criteria

Inclusion criteria	Exclusion criteria
1. Must be at least 20 years old. Capable of giving written informed consent.	1. Known coronary artery disease or unstable angina within the past 3 months.
2. Agrees to comply with the study protocol.	2. Acute myocardial infarction within the past 6 months.
3. Known low extremity artery disease (documented by previous angiography or sonography) admitted for elective percutaneous transluminal angioplasty.	3. Known coronary artery disease having received percutaneous coronary intervention or bypass surgery within the past 6 months.
	4. Plans to do bypass surgery for known low extremity artery disease.
	5. Has been pregnant.
	6. Has documented active malignancy.
	7. Needs emergency percutaneous transluminal angioplasty.

### Eligibility criteria for investigating centers and those performing the interventions

The minimal requirements of the investigating centers are as follows: (1) a medical center or a regional hospital equipped with at least 500 acute care beds, (2) an experienced participating site where there is a good track record with respect to conducting clinical trials, and (3) a high-volume center with at least 500 PCI procedures and at least 100 PTAs each year. Those who are performing the interventions should fulfill both of the following eligibility criteria: (1) an experienced investigator who has a good track record with respect to conducting clinical trials and (2) an experienced operator with at least 75 PCI procedures and at least 50 PTAs each year.

### Blinding and randomization

Owing to the nature of the trial interventions, it will not be possible to blind the investigators at clinical trial sites, the participants, or the participants’ relatives. All other parties in the trial will be blinded. Those assessing biomarkers, single-nucleotide polymorphisms, micro-ribonucleic acids, and clinical endpoints are all blinded after assignment to interventions. Investigators conducting the statistical analyses will be blinded; the two intervention groups and one registry group will be coded as, for example, A, B, and C.

Eligible participants were randomly assigned to routine strategy or selective strategy by using unrestricted randomization and open label for allocation. Sealed envelopes for allocation concealment are provided. The allocation sequence is generated by [name]. Detailed information regarding the allocated group is given on cards contained in sequentially numbered, opaque, and sealed envelopes. These are prepared at the core coordinating center and kept in an appropriate location on each site. After enrollment of a participant, the appropriate numbered envelope is opened at the participating site. The information on whether the patient is to be a “routine” or “selective” case can be found on the card and this information then is given to the coordinator of the core coordinating center. Then, the investigator and research nurse follow the intervention protocol according to the allocation assignment. If participants are not willing to be randomly assigned, they will be included in the registration group if they agree. This information should also be given to the coordinator of the core coordinating center. The enrollment will be closed if the target number of randomly assigned participants is reached.

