### Data management and monitoring

Electronic case report forms (CRFs) for the PIROUETTE-PTA trial are developed on the infrastructure of the Clinical Study Information System (CSIS) in cooperation between the coordinating investigator and a data manager at the Clinical Research Center of National Cheng Kung University Hospital. CSIS is the information management service provided by the Taiwan Clinical Trial Bioinformatics and Statistical Center, Training Center, and Pharmacogenomics Laboratory to facilitate the coordinating investigator in building up the electronic CRF system in investigator-initiated trials. This resource center is funded by the National Research Program for Biopharmaceuticals under grant support by the Ministry of Science and Technology (grant number 104-2325-B-002-033) and the Center for Systems and Synthetic Biology in National Yang-Ming University in Taiwan. Access to the CSIS will be possible around the clock every day and data can be entered continuously for all the randomly assigned patients. The coordinating investigator will have access to monitor the data input. If the entry is partially or completely missing or seems flawed on one or more randomly assigned patients, the coordinator will have the opportunity to contact the primary investigator in order to correct or complement data inputs to optimize the quality of the data. There are 13 CRFs to be filled on the CSIS at each indicated visit in the current study; Additional file 3 shows clinical data to be collected and recorded in more detail. The steering committee has access to the full trial dataset.

Original CRFs and source document will be kept on file and stored in numerical order and in a secure place with limited access at the participating site. All study-related records, materials, or documents are identified only by a coded identification number to keep participants’ confidentiality, whereas any records that should contain names or other personal identifiers, such as informed consent forms, will be stored separately from study records. An inspection team will select participating sites to monitor quality of the study at audit visits. Besides, a subset of the original CRFs will be requested for quality control during study. When a form is selected, the participating site staff will send the copy to the data management committee for inspection and double data entry.

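### The site opens the envelope before the coordinating center hears of the patient, and no stated step fixes willingness to be randomized beforehand, although a registration group is open to the same patients

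*Protocol article*

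**What the plan says.** All of the allocation procedure is in the section Blinding and randomization of the Protocol article.

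- Custody: the allocations are on "cards contained in sequentially numbered, opaque, and sealed envelopes". On storage: "These are prepared at the core coordinating center and kept in an appropriate location on each site".
- Opening: "After enrollment of a participant, the appropriate numbered envelope is opened at the participating site".
- Notice: once the card has been read, "this information then is given to the coordinator of the core coordinating center".
- Registration group: "If participants are not willing to be randomly assigned, they will be included in the registration group if they agree". On reporting these patients: "This information should also be given to the coordinator of the core coordinating center". Neither sentence gives a time point relative to the opening of an envelope.

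The same section says that site investigators, participants and relatives cannot be blinded, that randomization is unrestricted, and that enrollment closes when the target number of randomized participants is reached. The section Participants and eligibility draws both groups from one pool; the study will "consecutively enroll about 700 (450 randomly assigned and estimated 250 in registration strategy) eligible patients".

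**The concern.** In the order given, the center's first stated contact about a randomized patient comes after unblinded site staff know the allocation. A non-randomized group stands open to the same eligible patients, and the section Allocation and intervention has them managed by consensus as in usual care. A patient who balks on hearing the card, or an operator who prefers the other strategy, thus has somewhere to go. No bad faith is needed: a patient who withdraws agreement at that moment could sincerely be described as unwilling to be randomized.

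If this happens more in one arm than in the other, and the patients who leave differ in risk from those who stay, the randomized comparison is biased at entry. The planned intention-to-treat analysis does not help, because the patient does not appear in the randomized set. Blinded endpoint adjudication does not help either, because the bias arises before follow-up.

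**Working it through.** **Step 1. Does the wording close the gap?** Opening follows enrollment. If enrollment meant a recorded commitment to be randomized, the order would be safe. But the Abstract and Participants and eligibility use the same verb for registration patients: 700 enrolled = 450 randomized + about 250 registered (250/700 = 36%). Enrollment therefore does not by itself mean that randomization has been accepted.

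**Step 2. The plan's own figure.** Inputs from Power estimation and sample size calculation: 40% vs 24%, margin 5 points, one-sided alpha 0.05, power 80%, dropout 4%.

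n per arm = [0.40×0.60 + 0.24×0.76] × (1.645 + 0.842)² / (0.16 − 0.05)² = 215.8, so 216 per arm and 432 in total; 432/0.96 = 450. The stated 432 and 450 are reproduced, and this point does not change them.

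**Step 3. Possible size, by assumption only.** The article gives no diversion rate and no risk for diverted patients. Assume that half of the patients are at higher risk, with event risks of 50% vs 30% or 60% vs 20% (mean 40% in both cases). A fraction d of the higher-risk patients allocated to one arm is moved to the registration group and replaced, since enrollment runs until the randomized target is met. For simplicity 216 are analyzed per arm.

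Rate left in that arm = [0.5(1 − d)·r_high + 0.5·r_low] / [0.5(1 − d) + 0.5]

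For example, d = 0.10 with 50%/30%: (0.225 + 0.150)/0.95 = 39.5%, a shift of 0.5 points. With d = 0.20 and 60%/20%: (0.24 + 0.10)/0.90 = 37.8%, a shift of 2.2 points.

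Rejection probability = Φ[(difference − margin)/SE − 1.645], with SE² = [p₁(1 − p₁) + p₂(1 − p₂)]/216.

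| d | Risks, high/low | Moved, of 225 | Shift (points) | Error vs zero, no true effect, routine arm depleted | Error vs 5-point margin, same case | Power vs margin, true 40% vs 24%, selective arm depleted |
|---|---|---|---|---|---|---|
| 0 | either | 0 | 0 | 5.0% | 0.34% | 80.0% |
| 0.10 | 50/30 | about 11 | 0.5 | 6.3% | 0.47% | 76.6% |
| 0.10 | 60/20 | about 11 | 1.1 | 7.8% | 0.65% | 72.9% |
| 0.20 | 50/30 | about 22 | 1.1 | 7.9% | 0.67% | 72.5% |
| 0.20 | 60/20 | about 22 | 2.2 | 12.1% | 1.26% | 63.8% |

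The rows with d above zero correspond to 5% and 10% of one arm.

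**Step 4. Would arm sizes reveal it?** Under unrestricted 1:1 randomization of 450, the 95% range for one arm is 225 ± 1.96 × √450/2, about 204 to 246. Losing 10% of one arm's allocations gives 450 × 0.9/1.9 = 213 vs 237, inside that range. Arm sizes alone would not show diversion of this order.

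**The case against.** The case on the other side has real weight.

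- **The plan does not permit it.** The registration group is for people unwilling to be randomized, not for people who dislike their allocation. Diversion after opening would be a breach. This stands; the point is that the stated order does nothing to prevent or date such a breach.
- **There is a trail.** A reader might infer that the center could never distinguish a refusal before opening from one after it. The documents do not support that. The envelopes are numbered in sequence and prepared at the center, so a diverted patient leaves a used number without a randomized participant, and reconciliation could find it. The article describes audit visits to selected sites and inspection of a subset of case report forms, but no envelope reconciliation.
- **The article is condensed.** The full protocol may hold an enrollment log or a reconciliation rule, and Table 2 lists a form at V0. This is fair, and the absence of those details is not the point. The order of opening first and notifying afterwards is stated outright.
- **The magnitudes are assumed.** This stands in full. The primary analysis tests for a reduction of more than 5 points, so in these scenarios the false-positive rate against the margin stays near 1% or below; the inflation applies to a comparison against zero. The effect can also run against the routine strategy.

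**Conclusion.** The point holds as a weakness in a stated procedure that can be cheaply improved. Nothing in the documents shows that diversion has occurred or is likely.

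With 5 to 10% of one arm diverted, all at higher risk, the difference moves by roughly 0.5 to 2 points. Depletion of the routine arm gives a false benefit; depletion of the selective arm lowers power from 80% to between 77% and 64%. All of this rests on the assumed risk split and diversion rates.

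A reader might go further and suppose that heavy diversion could pass unnoticed because the registration group is large. The article does not support that. Losing a fifth of one arm's allocations would leave 450 × 0.8/1.8 = 200 vs 250 randomized, outside the 204 to 246 range (z = 25/10.6 = 2.4), and a run of orphaned envelope numbers besides.

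**What to change.** Move the existing contact with the coordinator ahead of the opening, and say so in the protocol:

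1. Before any envelope is opened, the site logs the participant and the documented choice, randomize or register, with the coordinator or in the electronic system. On access to that system the section Data management and monitoring says: "Access to the CSIS will be possible around the clock every day". It describes data entry there for randomized patients, so a short entry for this choice may have to be added.
2. Every opened envelope counts as a randomized participant in the intention-to-treat set, whatever happens next.
3. Registration entry is allowed only if unwillingness was logged before opening.
4. Envelope numbers, including those already opened, are reconciled with the log at the planned audit visits.

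The sample size does not change. The cost is a short wait at the site and a formal amendment, which the section Study design says the institutional review boards of the coordinating hospital and the other sites must approve. Recruitment is already open, so the change cannot protect patients already randomized; for them only the reconciliation in item 4 is available.
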